### Adverse events

Before the start of treatment and after 4 weeks of treatment a medical history will be recorded for each patient, and standard laboratory examinations and specific laboratory investigations will also be performed. The standard laboratory examinations include: hematologic parameter assessments (hemoglobin, red blood cells, platelets, and white blood cell counts); urinalysis (proteins, red blood cell and white blood cell biochemical assessment (serum electrolytes)); indices of renal function (creatinine, urea) and hepatic function (alkaline phosphatase, aspartate aminotransferase, alanine aminotransferase, and gamma-glutamyl transpeptidase); serum calcium; and an electrocardiogram. The specific laboratory investigations mainly include serum cytokine levels.

All adverse events will be collected and graded for severity and potential relation to the treatments in the study by assessors at every visit. Safety evaluations include the incidence of treatment-induced or serious adverse events, dropout because of adverse events, and changes from baseline of the PASI score and laboratory parameters. Patients will be also asked about other adverse effects of auricular therapy such as faintness, nausea, and vomiting. In case of severe adverse effects, auricular therapy will be discontinued immediately.

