### Randomization

Eligible patients will be randomly assigned in a 1:1 ratio to one of the two groups (the treatment group who receive auricular acupressure plus calcipotriol betamethasone ointment or the control group who receive calcipotriol betamethasone ointment) at the second visit through central randomization. Equal randomization will be conducted using a computer-generated random allocation sequence through the stratified block randomization method of the SAS software (version 9.12; SAS Institute, Inc., Cary, NC, USA) with a block size of 4 by the Key Unit of Methodology in Clinical Research (KUMCR) of Guangdong Provincial Hospital of Chinese Medicine. Allocation concealment will be ensured since the randomization code will be released by the Interactive Web Response System for Chinese Medicine Trials (IWRS-CMT), which is a verified online randomization facility established by the KUMCR (http://www.gztcmgcp.net/sjxt /login.asp). Following this, the participants will be randomly allocated to the two different groups. The practitioners will be aware of the allocation arm according to the different medical procedures. However, the evaluation of participants and the analysis of the results will be performed by physician assessors and statisticians who are blinded to the group allocation [32].

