### Outcome

#### Primary outcome measurement

The primary outcome measure in the trial is relapse rate in the treatment period and follow-up period. Relapse is defined as losing 50% of the improvement obtained from treatment once the treatment is stopped [40]. The PASI will be assessed every visit during the treatment period and the follow-up period. Meanwhile, patients will be required to report the emergence of a variety of conditions at any time in the study period. Assessors will evaluate the PASI score on the same or closest day. Target lesions will be recorded as digital photographs by single-lens reflex (SLR) cameras at every visit.

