### Statistical analysis

All analyses will be performed with PASS Statistics and SAS 9.2 software by a statistician who is blinded to the random allocation of groups. An intent-to-treat (ITT) basis statistical analysis with a 95% confidence interval will be performed using multiple imputations. The major imputation is multiple imputation by chained equations (MICE). The ITT analysis will include all patients who are randomized [43]. Safety analysis will be undertaken by analyzing the frequency of adverse events which are suspected as related to the treatment. Planned subgroup analyses include those based on the type of TCM syndromes and severity of psoriasis. The various parameters observed will be compared using a Chi-square test for noncontinuous variables (i.e., the primary outcome relapse rate) and *t* test and analysis of variance (ANOVA) for continuous variables. In order to distinguish the treatment effect and time effect, the repeated measures ANOVA change from baseline will be performed for the different time point assessments. Statistical significance is established at *P* < 0.05. No formal interim analysis is planned.

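### Grading each adverse event's relation to treatment is assigned to assessors, the term used for the blinded PASI raters, and the stated safety analysis depends on that judgement

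*Protocol article*

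**What the plan says.** All references are to the protocol article.

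- **Randomization.** Treating staff are open: "The practitioners will be aware of the allocation arm according to the different medical procedures". Rating and analysis are meant to be blind: "the evaluation of participants and the analysis of the results will be performed by physician assessors and statisticians who are blinded to the group allocation".
- **Primary outcome measurement.** Relapse is the loss of half the improvement gained on treatment, measured on PASI. "The PASI will be assessed every visit during the treatment period and the follow-up period". When patients report a change between visits, "Assessors will evaluate the PASI score on the same or closest day".
- **Auricular acupressure treatment.** Seeds are fixed to both ears in the intervention arm only. The control arm receives ointment alone, without a sham.
- **Adverse events.** "All adverse events will be collected and graded for severity and potential relation to the treatments in the study by assessors at every visit". Further on: "Patients will be also asked about other adverse effects of auricular therapy such as faintness, nausea, and vomiting". The sentence does not say who asks. The section also lists safety evaluations: treatment-induced or serious events, dropout because of adverse events, and changes in PASI and laboratory values.
- **Statistical analysis.** "Safety analysis will be undertaken by analyzing the frequency of adverse events which are suspected as related to the treatment".

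**The concern.** Patients and practitioners know the allocation, so the blinded assessor is the main protection for an endpoint that depends on a rater's judgement. Judging whether an event is related to the study treatments normally requires knowing which treatments the patient received. Talking to patients about ear-treatment effects also gives them an opening to disclose their arm. If the person doing this also scores PASI, at that visit or a later one, the score is no longer protected.

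The second part concerns safety. A comparison that counts only events judged to be related is a comparison of attributions. In an open trial where one arm has an additional treatment to blame, equal underlying event rates can give unequal counts.

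**Working it through.** **1. The role, section by section.**

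| Section | Who | Task | When |
|---|---|---|---|
| Randomization | physician assessors | evaluate participants, blinded | not stated |
| Primary outcome measurement | assessors | score PASI | every visit, and after patient reports |
| Adverse events | assessors | collect events; grade severity and relation to the treatments | every visit |
| Adverse events | not named | ask about effects of auricular therapy | not stated |

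The term is shared, both tasks recur at every visit, and no separate safety rater is described. That supports an assignment of both tasks to one named role. It does not establish that the same individuals do both.

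**2. Can the blind and the causality grade coexist?** There are two cases.

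- The grader stays blind. Relation to acupressure then has to be judged without knowing whether the patient had any.
- The grader learns the arm. The grade is then informed, but any PASI score by that person is exposed.

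The article does not say which case applies and gives no order of tasks within a visit.

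**3. How near the threshold a rating can lie.** Relapse score = lowest PASI + 0.5 × (baseline − lowest PASI).

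- Assumed patient, 10 falling to 3: 3 + 0.5 × 7 = 6.5.
- Entry floor of 7 (Inclusion criteria) with a 50% response: lowest 3.5; 3.5 + 0.5 × 3.5 = 5.25, a margin of 5.25 − 3.5 = 1.75 points.

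A rating shift of about one point can decide relapse for a patient near the threshold. This holds for any responder endpoint of this type. It shows sensitivity, not bias.

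**4. The plan's own sample size (background only).** Inputs from Sample size: 82% against 62%, two-sided α = 0.05, power 0.80, pooled Z test.

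n = [1.96·√(2 × 0.72 × 0.28) + 0.8416·√(0.82 × 0.18 + 0.62 × 0.38)]² / 0.20² = (1.2445 + 0.5210)² / 0.04 = 77.9, so 78 per arm.

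The plan states 77, at which power is 79.5%. Allowing for 15% loss, 77 / 0.85 = 90.6, so 91, against 90 stated. The plan's figures reproduce to within one patient per arm, and the point does not depend on them.

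**5. What a rating bias would do, if there were one.** Assume no true effect, 77 per arm, 82% relapse in control, and biased scoring that lowers recorded relapse in the intervention arm by m. The chance of a falsely significant benefit is Φ[(m − 1.96·s₀)/s₁], with s₀ the pooled and s₁ the unpooled standard error.

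| m | s₀ | s₁ | Chance |
|---|---|---|---|
| 0.05 | 0.0651 | 0.0649 | about 12% |
| 0.10 | 0.0678 | 0.0673 | about 31% |
| 0.15 | 0.0702 | 0.0692 | about 57% |

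The nominal rate in that direction is 2.5%. The values of m are assumptions; the document gives none.

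**6. The safety filter.** Let r be the true event rate, equal in both arms; a the chance that an event is attributed to ointment; b the chance that one not so attributed is put down to acupressure by a grader who knows the arm. If a is the same in both arms:

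- control count rate = r·a
- intervention count rate = r·[a + (1 − a)·b]

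The difference, r·(1 − a)·b, is above zero whenever b > 0 and a < 1, although the true rates are equal. If graders are blind, b no longer follows the arm and the difference largely disappears.

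**The case against.** The case on the other side is substantial.

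- **Same people?** A reader might infer that the PASI raters must also grade causality, so that the blind is broken. The article does not say so. The link rests on a shared word, and Data collection separately mentions a certificated clinical researcher who checks outcome records. A condensed article may leave the division of roles to the full protocol. This stands as a limit on the claim. Even so, the article assigns the causality task to a role it elsewhere calls blinded, and that wording needs correcting.
- **Does the questioning unblind?** A fixed question about faintness, nausea and vomiting put to every patient reveals nothing by itself, and no asker is named. That stands. The exposure comes from answers that mention the ears or seeds, and from the causality judgement.
- **Timing.** Seeds come off on the morning of day 6, so ears may be bare at the next weekly visit, and relapse is counted mainly after treatment stops. Both points reduce the risk. They do not remove it: an arm learned during treatment is still known in follow-up, and the improvement against which relapse is measured is scored during treatment.
- **Only related events kept?** A reader of Statistical analysis alone might infer that all other safety data are dropped. The Adverse events section contradicts this: all events are collected, and serious events, adverse-event dropouts and laboratory changes are evaluated. Data management also gives safety data to the monitoring committee. What remains is that the two sections differ and neither plans an all-event comparison by arm.
- **Zero related events in control?** A reader might infer that the control count is zero by construction. It is not: controls receive the ointment, to which events can be attributed, and the plan proposes no comparison of acupressure-attributed counts.

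**Conclusion.** The point holds in a limited form. The article gives causality grading to assessors, its term for the blinded PASI raters, in an open trial with no sham, and sets out no safeguard between the two tasks. That is a route to detection bias in the relapse outcome. It is not evidence that bias has occurred. Its size cannot be derived from the document, and the 12%, 31% and 57% figures show only what assumed biases of 5, 10 and 15 points would do.

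The stated safety analysis rests on a judgement that can differ by arm if graders know the allocation. Statistical analysis and Adverse events also disagree on which events are evaluated and must be reconciled. The conclusion assumes that the shared term means a shared role and that the full protocol does not already separate the tasks.

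**What to change.** 1. At each visit, complete and lock the PASI and BSA ratings before any adverse event questioning and before seeds are applied.
2. Have causality graded by existing unblinded study staff who do not rate PASI, and withhold that information from the raters. These need not be the acupressure therapists: the article describes them treating only the intervention arm, so it cannot be assumed that they already see every control patient.
3. Reconcile Statistical analysis with Adverse events. Compare all adverse events and all serious adverse events by arm regardless of attribution, with events suspected to be treatment-related as a secondary table.

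**Cost.** A visit-order and CRF instruction, some reassignment of existing staff at follow-up visits, and one extra table. Graders who know the arm may attribute events differently by arm, which is why the all-event comparison should come first. The sample size does not change.

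**Reach.** Trial status reports 154 of 180 recruited, so the role split can protect only the remaining 26 patients and visits still to come. Because all events are already to be collected, the all-event comparison can cover every participant.

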**Methods and analysis:**

This on-going study is a two-arm parallel, assessor-blinded, randomized controlled trial in which 180 participants with psoriasis will be recruited and then randomly allocated into two groups in a 1:1 ratio. Equal randomization will be conducted using a computer-generated random allocation sequence. Participants in the intervention group will receive auricular acupressure treatment once per week for 4 weeks, and calcipotriol betamethasone ointment for topical use once daily for 4 weeks. Participants in the control group will receive only calcipotriol betamethasone ointment treatment once daily for 4 weeks. All patients will be followed up for 12 weeks. The primary outcome is relapse rate. The secondary outcomes include time to relapse, rebound rate, time to new onset, Psoriasis Area and Severity Index score improvement rate, body surface area affected, a visual analogue scale, and Dermatology Life Quality Index. Cost-effectiveness analysis will be carried out from a health and community care provider perspective.

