### Sample size

There is a growing body of research evaluating the effect of auricular acupressure for various diseases. However, there is still a lack of studies evaluating the effect of auricular acupressure on psoriasis. There is no previous study on which to base the sample size calculation. Thus, we used the primary outcome relapse rate to determine a sample size calculation. Based on the study of Menter et al. [42], the relapse rate of calcipotriol betamethasone ointment topical therapy after 4 weeks of treatment and 4 weeks of follow-up is 82%. We assume that the relapse rate of auricular acupressure therapy combined with calcipotriol betamethasone ointment topical therapy for psoriasis in week 12 is 20% less than topical therapy alone and that the relapse rate of calcipotriol betamethasone ointment topical therapy is 82%. On the basis of this hypothesis, and in order to compare the two groups for a significance level α = 0.05 and a power 1 – β = 0.80, we calculated the sample size by PASS statistics software (version 11.0.10; NCSS LLC., Utah, USA); 77 patients with psoriasis would have been required in each group to achieve 80% power to detect a difference between the group proportions of −0.2. The test statistic used is the two-sided *Z* test with pooled variance. The significance level of the test is targeted at 0.05. Considering 15% loss to follow-up, 90 patients are needed in each arm, totaling 180 patients in all.

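### Faintness, nausea and vomiting are prompted for as effects of a therapy that only one arm receives; the protocol should put the same neutral question to both arms

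*Protocol article*

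**What the plan says.** The Adverse events section sets out two layers of collection. The first is general and has no arm restriction: "All adverse events will be collected and graded for severity and potential relation to the treatments in the study by assessors at every visit". The second is a specific prompt: "Patients will be also asked about other adverse effects of auricular therapy such as faintness, nausea, and vomiting". That sentence gives no arm and no visit schedule. The sentence after it concerns discontinuing auricular therapy, which can apply to the intervention arm only.

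The abstract describes the comparator: "Participants in the control group will receive only calcipotriol betamethasone ointment treatment once daily for 4 weeks". There is no sham procedure. The Randomization section says that evaluation and analysis are "performed by physician assessors and statisticians who are blinded to the group allocation".

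The Statistical analysis section states how adverse events are used: "Safety analysis will be undertaken by analyzing the frequency of adverse events which are suspected as related to the treatment". The Adverse events section also lists serious adverse events, dropout because of adverse events, and changes from baseline in PASI and laboratory values as safety evaluations.

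**The concern.** The prompted symptoms are defined as effects of a treatment that control patients do not get. Staff who follow the wording literally have no reason to put the question to a control patient. A control patient who is asked in those terms can fairly answer that it does not apply, because patients know whether seeds were stuck to their ears. No equivalent prompt is written for the ointment-only arm.

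Faintness, nausea and vomiting are non-specific and occur without any treatment. Only the contrast with the control arm can separate an effect of acupressure from background, and that contrast needs the same questioning in both arms. Safety of the add-on is a stated aim in the abstract. If questioning differs by arm, an excess of these symptoms under acupressure could come from the questioning alone, and no later analysis can recover symptoms that were never asked about.

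**Working it through.** **Step 1. The text, side by side.**

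| Question | What the article states |
|---|---|
| Who is prompted? | Patients; no arm named |
| What defines the prompt? | Effects of auricular therapy |
| Who receives that therapy? | Intervention arm only; no sham |
| Is there a matching control prompt? | None stated |
| Are general events collected in both arms? | Yes, all events, by assessors, at every visit |
| Are assessors blinded? | Yes, according to Randomization |

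Rows 2 to 4 point towards prompting in one arm. Rows 1, 5 and 6 point towards asking everyone. The wording does not settle it.

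**Step 2. The plan's own figure.** The article states no adverse-event rate, so there is none to reproduce. The only planned figure used here is the arm size. For 82% against 62%, two-sided 0.05, 80% power and pooled variance, the calculation gives 78 per arm against the stated 77 (power at 77 is 79.5%). Adding 15% loss gives 77 / 0.85 = 90.6, so 91, against the stated 90. These agree closely enough, and 90 per arm is used below.

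**Step 3. What one-arm prompting would do.** Assumptions, none of them from the article:
- the true incidence p of a symptom is the same in both arms;
- the prompted arm records all of it, at rate p;
- the unprompted arm records a fraction c, at rate c × p, with c from 0.3 to 0.8.

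The false excess is p − cp = p(1 − c). The apparent risk ratio is p / (cp) = 1/c, which is 1/0.8 = 1.25 up to 1/0.3 = 3.3 at any incidence. False significance is the probability that a pooled two-sided chi-square test at 0.05 rejects. It is found by exact enumeration of two independent binomials, X ~ Bin(90, p) and Y ~ Bin(90, cp), summing the joint probabilities of all pairs with |z| > 1.96.

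| True incidence p | False excess, c = 0.8 to 0.3 (points) | Rejection, c = 0.3 | c = 0.5 | c = 0.8 | c = 1 (equal) |
|---|---|---|---|---|---|
| 2% | 0.4 to 1.4 | 6.3% | 4.6% | 3.5% | 3.6% |
| 5% | 1.0 to 3.5 | 23.9% | 12.2% | 5.2% | 4.2% |
| 10% | 2 to 7 | 47.6% | 24.0% | 7.5% | 5.1% |
| 20% | 4 to 14 | 82.3% | 46.9% | 10.5% | 4.9% |

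For example, at p = 10% and c = 0.3 the expected counts are 90 × 0.10 = 9.0 against 90 × 0.03 = 2.7, with no true difference. At 2% incidence and 80% capture there is no inflation. If both arms are asked the same question in the same way, c is the same for both and the false excess is zero.

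**Step 4. What the table leaves out.** It counts every occurrence of a symptom. The planned safety analysis counts only events suspected as related to treatment, and the article does not specifically plan a chi-square test on these three symptoms. The table therefore shows the size of the ascertainment effect before that filter, not the error rate of a planned test.

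**The case against.** A reader might infer that control patients rely on volunteering these symptoms and that the safety comparison is therefore biased. The article does not say so. It names no arm for the prompt and has assessors collect all events at every visit in both arms. Assessors who are truly blinded cannot prompt by arm, which fits better with asking everyone. This objection stands, and the bias is conditional.

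A reader might also infer that event frequency is the only safety contrast. It is not: serious events, dropouts for adverse events and laboratory changes are listed too, and none depends on this prompt.

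The larger percentages come from assumed incidences of 10% and 20%. At 2% the effect nearly vanishes. The related-events filter is also a separate asymmetry: a control patient's nausea counts only if suspected as related to the ointment, so equal questioning alone would not give an equal comparison. Both points stand; the second shapes the fix.

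Any bias would overstate the harm of the add-on rather than hide it. That is true and lowers the stakes, though a spurious signal still misinforms a stated aim.

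Finally, visit-form detail usually belongs to the case report form and full protocol, which are not shown. That would answer a complaint about something missing. Here the article states an elicitation rule and ties it to one arm's treatment. Asking everyone in those words would still not give comparable answers from control patients.

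**Conclusion.** The point holds in conditional form. The prompt is worded around a therapy that one arm receives, and nothing in the article says that both arms get the same question. If it is applied to acupressure patients only, the frequency of faintness, nausea and vomiting is biased against acupressure. Whether that happens cannot be told from the text, and the size cannot be known without event rates. Under the stated assumptions the effect runs from negligible at 2% incidence with high unprompted capture to dominant at 20% with low capture.

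This is a minor improvement to safety ascertainment, worth making because it costs almost nothing. The primary outcome and the sample size are not affected.

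**What to change.** Reword the prompt under Adverse events so that one identical symptom question, covering faintness, nausea and vomiting and making no mention of auricular therapy, is put to every patient in both arms at every visit. State that these three symptoms will be compared between arms by frequency regardless of judged relatedness, alongside the planned analysis of suspected-related events. Effects local to the ear can still be described in the acupressure arm alone.

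The article reports 154 of 180 patients already recruited, so a new question would cover the remaining 180 − 154 = 26 patients (about 13 per arm) and any still in follow-up. If earlier patients were prompted in one arm only, the report should say so as a limitation of this comparison. A retrospective split into prompted and spontaneous events is possible only if the case report form recorded how each event was elicited, which the article does not say.

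The cost is a short amendment to the wording and a line on the visit form, at visits that already take place. The downside is a slightly longer control visit and a higher recorded event rate in the control arm.
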